**Fig. 1 Fig1:**
[figure not shown]
Flow chart of the study process

### Sample size calculation

Using a type I error of 5% (*α* = 0.05) and a type II error of 20% (*β* = 0.20, power = 80%), and serum HDL-C concentrations as the key variable, the sample size in this study was calculated using the following formula, which has been proposed for parallel clinical trials:$$n=\frac{2\left[{\left({\textrm{Z}}_{1-\frac{\alpha }{2}}+{\textrm{Z}}_{1-\beta}\right)}^2\times {\upsigma}^2\right]}{{\textrm{d}}^2}$$

*n* = sample size for each group.

*σ* = The variance (SD) for mean HDL-C concentrations was as 3.5, which was calculated using the average SDs reported for serum HDL-C in Rajaie et al. study [35].

*d* = The minimal clinically important difference for HDL-C was set at 2.5, based on previous research [38].

Overall, using this formula and assuming a 10% drop-out rate in each group, we will require a sample size of 35 subjects in each group.

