### Assessment of variables

A standard questionnaire will be used to collect data on participants’ age, ethnic origin, marital status, educational level, disease history, family history of disease, medication use, and history of COVID-19 and type of vaccination. We will also measure primary outcomes including serum lipid profile concentrations, fecal bacterial load, and glucose levels, as well as secondary outcomes including anthropometric measurements and blood pressure at the beginning of the study, end of the phase I (3 months), and end of the phase II (6 months).

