### Statistical analysis

All statistical analyses will be carried out using the SPSS software version 25 (SPSS Inc., Chicago, IL, USA). For addressing non-adherence, the intention-to-treat (ITT) analysis will be applied [41]. Moreover, we will apply the last observation carried forward method (LOCF) to handle missing values [42]. In order to determine the normal distribution of variables, we will use the Kolmogorov-Smirnov test, histogram, and Q-Q plot. We will log transform (ln) the data, if necessary, to achieve normal distribution. Data will be presented as mean ± standard deviation (SD) for continuous variables and as percentages for categorical variables. Chi-square test and independent samples *t*-test will be used for comparing continuous and categorical variables between the two groups, respectively. We also will use the paired-sample *t* test for within-group comparisons. Repeated measures analysis of variance will be employed to determine the impact of the intervention on the outcome variables. These analyses will examine the effects of the intervention, time, and the interaction between time and intervention. Any potential differences in baseline levels of outcome variables, dietary intakes, and physical activity will be controlled in these analyses. Statistical significance will be defined as *P* values less than 0.05.

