## Strengths and limitations

This is the first clinical trial examining the effect of a moderately restricted carbohydrate diet on the composition of gut microbiota and several metabolic parameters in patients with MetS. It should be noted that the intervention is low-cost and no extra charge would be imposed to patients. Stratified block randomization will be used to match patients based on a number of confounding variables that may influence the outcomes. Additionally, participants will be recruited through public announcements. Thus, all volunteers may be encouraged to adhere to dietary recommendations. Another potential strength of the study is the measurement of gut microbiota composition and biochemical parameters not only during the intervention but also after the intervention, during the maintenance phase. Dietary intakes and physical activity will be evaluated during both phases of the study as well.

There are several limitations to this study that should be considered. The major limitation of the current trial is the small number of bacterial species and biochemical parameters that will be examined. Moreover, we are concerned about gut microbiota changes during sample collection. In order to prevent this, stool samples will be collected in the laboratory and immediately frozen at − 80 °C. In addition, we strive to have all stool samples delivered to the laboratory within 4 h of collection. Nevertheless, several samples may arrive within more than four hours. Even though biomarkers could provide more accurate measures for validating dietary records, we will not use them to evaluate diet compliance due to financial constraints. This study will be conducted during the COVID-19 pandemic, which could increase the number of participants who are lost to follow-up.

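### The 10% drop-out allowance assumes lost women leave the analysis, but ITT with LOCF keeps them in, so 80% power holds only under conditions the plan does not state

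*Protocol article*

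**What the plan says.** Three parts of the protocol article bear on this.

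- **Sample size calculation.** The size rests on "serum HDL-C concentrations as the key variable", with two-sided 5% type I error, 80% power and an SD of 3.5. On the effect: "The minimal clinically important difference for HDL-C was set at 2.5, based on previous research". Then, "assuming a 10% drop-out rate in each group, we will require a sample size of 35 subjects in each group". The drop-out rate has no time point, and the section does not say whether 2.5 applies to completers or to all randomised women.
- **Statistical analysis.** Non-adherence is handled by ITT, and "we will apply the last observation carried forward method (LOCF) to handle missing values". The intervention effect is tested by repeated-measures ANOVA, with baseline levels of the outcome controlled.
- **Assessment of variables.** Outcomes are taken "at the beginning of the study, end of the phase I (3 months), and end of the phase II (6 months"). Biochemical assessments places the last blood sample at month 9. Between baseline and month 3 there is no HDL-C value.

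Exclusion criteria pulls the other way on who is analysed. It says that women who will not continue and adhere poorly, and women who catch COVID-19 during the intervention, will be excluded.

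**The concern.** A drop-out allowance replaces women who are missing from the analysis. It restores the target power when those who remain show the full planned difference. LOCF works differently: it keeps the number analysed at 35 per arm but gives each early loss a value from before the diet began. The denominator is preserved and the expected difference shrinks. Dividing by 0.90 does not compensate for that.

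The 80% is the only power figure in the article, and a non-significant HDL-C result would be read against it. The article also expects COVID-19 to affect retention, "which could increase the number of participants who are lost to follow-up", and dilution worsens faster with loss than a smaller analysed sample does.

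**Working it through.** **Inputs** (Sample size calculation unless noted): two-sided α = 0.05, power 80%, d = 2.5, SD = 3.5, drop-out 10% per arm, 35 per arm. ITT with LOCF is from Statistical analysis, and the measurement times are from Biochemical assessments.

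**1. The plan's own figure.** n = 2(1.960 + 0.842)² × 3.5² / 2.5² = 30.77, rounded up to 31. Then 31/0.90 = 34.4, rounded up to 35. The stated size reproduces.

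**2. What the allowance presumes.** With 10% lost and not analysed, 31.5 women per arm remain at the full 2.5. SE = 3.5 × √(2/31.5) = 0.882. Power = Φ(2.5/0.882 − 1.960) = 80.9% by the plan's normal approximation, or 79.7% by t-test.

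**3. What LOCF does at month 3.** Assume the 10% is lost before month 3, equally in both arms and unrelated to outcome, and that 2.5 is the difference in women who complete phase I. The expected difference is 0.90 × 2.5 = 2.25 with 35 per arm. SE = 3.5 × √(2/35) = 0.837. Power = Φ(2.25/0.837 − 1.960) = 76.7%, or 75.5% by t-test. Mixing treated and undiluted-baseline values adds 0.10 × 0.90 × 2.5² = 0.5625 to the intervention-arm variance, which gives 75.8% and 74.6%. Holding 80% on these assumptions would take 30.77/0.90² = 37.98, so 38 per arm.

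**4. Range of early loss** (unadjusted, 35 randomised per arm):

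| Lost before month 3 | LOCF, normal | LOCF, t | LOCF, t with mixture variance | Observed values, t |
|---|---|---|---|---|
| 0% | 84.8% | 83.8% | 83.8% | 83.8% |
| 5% | 81.0% | 79.9% | 79.4% | 81.8% |
| 10% | 76.7% | 75.5% | 74.6% | 79.7% |
| 15% | 71.9% | 70.7% | 69.3% | 77.3% |
| 20% | 66.7% | 65.4% | 63.7% | 74.7% |
| 30% | 55.2% | 54.1% | 52.0% | 68.7% |

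**5. With baseline adjustment.** Simulated trials (20,000 per setting, 35 per arm, SD 3.5 at both visits, 10% random loss before month 3, month-3 value regressed on arm and baseline). The correlations are assumptions, since the article gives none.

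| Baseline to month-3 correlation | LOCF | Observed values |
|---|---|---|
| 0 | 74% | 79% |
| 0.2 | 78% | 81% |
| 0.3 | 80% | 82% |
| 0.5 | 87% | 89% |
| 0.7 | 96% | 97% |

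Adjustment regains 80% under LOCF at a correlation of about 0.3, at 10% loss. Observed-value analysis has the higher power at every correlation tried.

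**6. If 2.5 is the ITT difference.** All 35 per arm count and no allowance was needed: 84.8% (normal) or 83.8% (t). Completers would then have to differ by 2.5/0.90 = 2.78.

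**The case against.** A reader might infer that the trial simply has 75% power where it claims 80%, or that 35 should have been 38. The documents do not support either flat statement.

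- **Timing of loss.** The 10% carries no time point and follow-up lasts nine months. A woman lost in phase II has a real month-3 value. If loss were spread evenly (an assumption), 10% × 3/9 = 3.3% would go before month 3, and unadjusted LOCF power would be 82.3% (normal) or 81.3% (t).
- **Meaning of 2.5.** It is given as a minimal clinically important difference and not as a completer effect. Read as the difference the ITT analysis should detect, the plan is conservative.
- **Planned analysis.** The 75–77% belongs to an unadjusted comparison, while the article plans to control baseline. A modest correlation removes the shortfall at 10% loss.
- **Exclusions.** If non-adherent and COVID-19-infected women really leave the analysis, the allowance is coherent and power is about 80%, but the analysis is then not the ITT that the article announces.
- **The SD.** If 3.5 were the SD of change, carried-forward zero changes would also shrink the variance, and power at 10% loss would be about 75–80% for an assumed control-arm mean change of 2.5 down to 0. The article words it as the SD of HDL-C concentrations.
- **Scale.** About one point of the gap between 75.5% and 80% comes from setting a t-test result against a normal-approximation target.

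All of this stands as a limit on size. The mismatch remains: the article fixes both the allowance and the missing-data rule, and no single reading makes both right. Nor does baseline adjustment cancel the cost of LOCF: at correlation 0.3 and 10% loss it gives about 80%, against about 87% with no loss.

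**Conclusion.** The point holds as an inconsistency between the drop-out allowance and the stated analysis. It is not an arithmetic error, and 35 per arm is correctly computed.

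The cost is modest and conditional. At 10% loss before month 3, equal between arms and unrelated to outcome, with 2.5 as the difference in phase I completers and no baseline adjustment, power is about 75–77%; at 20% loss it is about 64–67%. It is about 80% if early loss is about 5% or less, or if baseline is adjusted for and the correlation is about 0.3 or more at 10% loss. It is 84–85% if 2.5 is the ITT difference. The article states none of these conditions, so the 80% cannot be taken as the power of the analysis it describes.

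**What to change.** 1. Make the main HDL-C analysis a baseline-adjusted repeated-measures mixed model on the observed values of all randomised women, and move LOCF to a sensitivity analysis. This fits the 1/0.90 allowance, removes the dilution towards zero and adds no participants. The cost is reliance on a missing-at-random assumption and a little more analysis work.
2. If LOCF stays as the main method, state the 80% as conditional on the proportion lost before month 3 and on the assumed baseline to month-3 correlation. Do not insert a flat 75%, which would describe an unadjusted test the article does not name as its main analysis.
3. In Sample size calculation, say whether 2.5 is the difference in phase I completers or in all randomised women, and by when the 10% is expected to be lost.
4. Reconcile the exclusion of non-adherent and COVID-19-infected women in Exclusion criteria with the ITT statement in Statistical analysis, because this decides who counts as lost.

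Items 2 to 4 cost a few sentences.

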### Study design

A total of 100 women with metabolic syndrome will be screened according to the aforementioned inclusion criteria in the initial phase. After recruiting participants from online advertisements and social media, seventy women who meet the inclusion criteria will be included in the entire project. Patients will be enrolled using a stratified block randomization procedure with a block size of 4. Participants will be randomly assigned to the intervention or control groups based on stratification by age (20–30, 30–40, and 40–50 years) and BMI (25–29.9, 30–34.9, and > 35 kg/m^2^). First, we will enroll a woman in a stratum that meets the inclusion criteria. Following that, the second person matched based on these variables with the first one will be placed in the same stratum. Consequently, two participants with similar characteristics (for the aforementioned variables) would be in the same stratum (Supplementary file, section B). Finally, using a random allocation software, two subjects from the same strata will be randomly assigned to either moderately restricted carbohydrate diet (MRC) or normal weight loss (NWL) diet groups. The principal investigator ([name]) will enroll eligible women. All participants will sign a consent form before inclusion in the study, in which information about the prescribed diets, duration of the study, and contact information for the research team are provided. Study participants will be informed that the services given to them will be free of charge and that they can withdraw from the study at any time throughout the study. Each person will receive a booklet, including a pre-designed dietary plan containing a series of menus and recipes for breakfast, lunch, dinner, and snacks according to the prescribed diet. In the current trial, outcome assessors will be blinded to the intervention allocation. The study protocol for this clinical trial was registered with the Iranian Registry of Clinical Trials in advance (IRCT20210307050621N1). The flow diagram of the research process is presented in Fig. 2.

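### Randomisation is described in two ways that do not agree (fixed blocks of 4, and matched pairs), and each reading carries a conditional weakness that one clear scheme would remove

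*Protocol article*

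**What the plan says.** The Study design section of the protocol article gives two accounts of allocation in one paragraph.

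- **Blocks of 4.** "Patients will be enrolled using a stratified block randomization procedure with a block size of 4", with "stratification by age (20–30, 30–40, and 40–50 years) and BMI (25–29.9, 30–34.9, and > 35 kg/m^2". That is 3 × 3 = 9 strata.
- **Pairs.** A first eligible woman is enrolled into a stratum. "Following that, the second person matched based on these variables with the first one will be placed in the same stratum". A computer program then makes the draw: "two subjects from the same strata will be randomly assigned to either moderately restricted carbohydrate diet (MRC) or normal weight loss (NWL) diet groups".

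Blocking is also tied to matching under Strengths and limitations: "Stratified block randomization will be used to match patients based on a number of confounding variables".

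Further facts that bear on the point:

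- The number is fixed: "seventy women who meet the inclusion criteria will be included in the entire project".
- The principal investigator "will enroll eligible women".
- On blinding: "In the current trial, outcome assessors will be blinded to the intervention allocation". Nobody else is said to be blinded.
- The Intervention section has each woman taught her diet in an hour-long session.
- The pairing text refers to section B of the supplementary file, which is not at hand.

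**The concern.** A reader cannot tell from this paragraph how the women were randomised. The unit (one woman or two), the block size (4 or in effect 2) and the timing (on enrolment, or once a match is found) all differ between the two accounts.

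Two things are at stake. First, in an open diet trial at one hospital, a small block of known size can let the person who enrols anticipate the next allocation. Enrolment could then be influenced by the expected diet, and analysis cannot undo that. Second, the analysis should reflect the design: stratification factors if blocks were used, the pair if pairs were used. The Statistical analysis section plans independent-samples t-tests and repeated measures ANOVA, adjusted for baseline outcome levels, diet and physical activity. Whether that matches the design depends on which account is true.

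**Working it through.** **Inputs.** 70 women, 9 strata, block size 4 or pairs (Study design). Type I error 5%, power 80%, SD 3.5, difference 2.5, drop-out 10% (Sample size calculation).

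**The plan's own figure.** n = 2 × (1.960 + 0.842)² × 3.5² / 2.5² = 30.77, so 31 per group. 31 / 0.9 = 34.4, so 35 per group. The stated size reproduces and is not in question.

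**Are the two schemes different?** A block of 4 with two women per diet has 6 possible orders. In 2 of them the first two women get the same diet, so the probability is 2/6 = 1/3. In a pair split between the diets it is 0. The schemes differ if the pair is split. If the two women could both receive the same diet, the pair text adds nothing to the blocks of 4.

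**Predictability, assuming block size, stratum and earlier allocations are all known**

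- *Completed block of 4.* The fourth allocation is always known. The third is known if the first two agree (probability 1/3). Share certain: (1 + 1/3) / 4 = 1/3. Best-guess accuracy: (1/2 + 2/3 + 2/3 + 1) / 4 = 70.8%.
- *Completed pair, split and assigned one at a time.* The second is always known. Share certain: 1/2. Best-guess accuracy: (1/2 + 1) / 2 = 75%.
- *Pair randomised together after both are enrolled.* Neither allocation can be predicted.

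**Allowing for incomplete blocks, 70 women over 9 strata.** With strata of this size, the remainder after division by 4 is close to uniform on 0 to 3, and odd and even counts are about equally likely.

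- *Blocks of 4.* Expected complete blocks: (70 − 9 × 1.5) / 4 = 14.125, giving 14.125 × 4/3 = 18.83 certain allocations. Strata left with three women: 9/4 = 2.25, each adding 1/3, so 0.75. Total 19.58 / 70 = 28%.
- *Sequential pairs.* Expected complete pairs: (70 − 4.5) / 2 = 32.75. 32.75 / 70 = 47%.

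**Women without a partner.** The chance that a stratum with share p holds an odd number is [1 − (1 − 2p)^70] / 2. With p = 1/9 this is 0.50, so the mean is 9 × 0.50 = 4.5. Since 70 is even, the number of odd strata must be even (0, 2, 4, 6 or 8), so 4.5 is only an average. Simulation (8,000 runs) gave a mean of 4.5, a 5th to 95th percentile range of 2 to 6, and about a 0.4% chance of none.

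**Sensitivity.** An assumed uneven mix (age 15/30/55%, BMI 30/40/30%) gave nearly the same results: 28%, 47% and 4.5. Very sparse strata would lower the last figure; at p = 0.01 the chance of an odd count is about 0.38.

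**The case against.** The best defence is that the pair sentence only describes how women fill the strata, while blocks of 4 govern allocation. The text says the two are assigned to either diet, not one to each, and the matching remark under Strengths and limitations fits ordinary stratification. This reading is possible, and the missing supplementary section may confirm it. It removes the conflict but leaves a small, fixed, published block size. It also leaves the text about finding a second woman with no purpose.

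A reader might infer more than the documents support:

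- *That the enrolling investigator knew upcoming allocations, or that selection bias occurred.* The article does not say who generates or holds the list, or whether the enroller sees earlier allocations by stratum. A condensed article may leave list custody and concealment to the full protocol, so their absence is not counted here.
- *That 1/3 or 1/2 of all allocations are exposed.* Those shares apply to completed blocks with full knowledge of earlier allocations. Over the whole trial they are about 28% and 47%.
- *That four or five women will go unallocated.* This needs pairs randomised together and enrolment stopped at 70 whether or not women are matched. If the 70 are 35 complete pairs, unmatched women lie outside them. Blocks of 4 leave nobody unallocated.

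It is also fair that a fixed block of 4 is a common choice, and that adjustment for design factors may stand in an analysis plan that is not shown.

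**Conclusion.** The point holds as a conflict between two stated procedures, with consequences that depend on which was used. At most about 28% of allocations (fixed blocks of 4) or about 47% (split pairs assigned in sequence) could be deduced. Both figures assume knowledge of the block size, the stratum and earlier allocations. With pairs randomised together, predictability is nil, and an average of 4.5 of 70 women would lack a partner if enrolment stops at 70. These harms do not all apply at once. The documents do not show that any allocation was foreseen. The sample size is unaffected. The matter should be corrected because the method of randomisation cannot be determined from the text and the remedy is cheap.

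**What to change.** - State one scheme for any remaining enrolments: stratified permuted blocks of randomly varying size, with the sizes not disclosed to the person who enrols.
- Delete the text on waiting for a matched second woman.
- Report which scheme was actually used for women already randomised and, if pairs were used, whether they were assigned together or in sequence and what happened to unmatched women. The Trial status section expects recruitment to end in June 2022, so this may be the only part still open.
- Include the stratification factors in the analysis, or the pair if pairs were used.

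The cost is a change of wording, a new list for the remaining women, and slightly less exact balance within strata. Exact balance is not assured now either. With blocks of 4, about 9 × 3/4 = 6.75 strata end on an incomplete block, and the simulated difference between arms averages about 2 women (95th percentile 6).

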**Fig. 2 Fig2:**
[figure not shown]
Enrollment, interventions, and assessments at various points in time. The “X” denotes what has been accomplished during a specified time period. Mth, month

### Intervention

Participants will be randomly assigned into one of the two above-mentioned groups. During an hour-long discussion, each participant will be instructed on either the MRC diet or NWL diet. All participants will receive a calorie restricted diet based on their status of weight and BMI (300–500 kcal less than participant’s energy requirement). We will compute calorie requirements based on resting energy expenditure (using the Harris-Benedict equation) and physical activity levels. The main distinction between these two diets will be the proportion of calories derived from fats and carbohydrates. The MRC diet will be defined as 42–45% of energy from carbohydrates and 35–40% from fats, while the NWL diet will be defined as 52–55% of total calories from carbohydrates and 25–30% from fats. In fact, 10% of energy from carbohydrates in the MRC diet will be substituted with non-hydrogenated vegetable oils. Dietary protein intakes will be accounted for 15–17% of total energy across both dietary groups. The first phase of the study in which subjects will receive the aforementioned diets will last for 3 months. Then participants will enter the second phase, in which all participants will be followed for another 6 months on a weight-maintenance (WM) diet containing a normal proportion of macronutrients, including 52–55% carbohydrates, 27–30% fat, and 15–17% protein. The main objective of this phase is to determine whether the changes caused by the intervention will be maintained after six months. In addition, it will be determined if changes in gut microbiota persist after 6 months of a weight-maintenance diet and to what extent these changes might contribute to weight maintenance and the stabilization of metabolic variables after 6 months.

